**Manuscript word count: 2804**

**Abstract**

**Introduction**

A severe epidemic of COVID-19 has broken out in China and become a major global public health event. We focus on the ARDS-like changes and overactivation of Th17 cells in patients with COVID-19. To explore the safety and efficacy of ixekizumab against organ injury caused by the immune response to COVID-19.

**Methods and analysis**

The experiment is divided into two stages. In the first stage, the open trial, 3 patients with COVID-19 are treated with ixekizumab, and the safety and efficacy are observed for 7 days. In the second stage, 40 patients with COVID-19 are randomly divided into two groups at 1:1 for 14 days. Patients with COVID-19 aged 18-75 with increased IL-6 levels will be enrolled. Inclusion was initiated in June 2020. The primary outcome is pulmonary CT score, and the secondary outcomes are pulmonary function, clinical symptoms, the incidence of admission to the ICU, the incidence of noninvasive ventilation, 14-day etiological mortality, length of hospitalization, and laboratory examination. The trial will provide data on the efficacy and safety of ixekizumab and antiviral therapy for patients with COVID-19.

**Ethics and dissemination**

The Institutional Review Board of the Xiangya Hospital of Central South University approved the protocol. Results will be disseminated via journal articles.

**Trial registration number**

<http://www.chictr.org.cn/> with code ChiCTR2000030703.

**Strengths and limitations of this study**

This trial protocol first describes a pilot-randomized, evaluator-blind, and controlled clinical trial testing the safety and efficacy of ixekizumab and antiviral treatment in patients with COVID-19.

Possible limitation was that the sample size was not statistically estimated.

**Introduction**

Since December 2019, a serious epidemic of COVID-19 has broken out in China and has become a major global public health event ^[1]^. The World Health Organization officially named the pneumonia epidemic in Wuhan "Corona Virus Disease 2019" (COVID-19). At present, the main source of infection is patients infected by the novel coronavirus. Asymptomatic infection may also be a source of infection. Respiratory droplets and contact transmission are the main routes of transmission. The common signs of coronavirus infection are respiratory symptoms, fever, cough, shortness of breath and dyspnea ^[2]^. In more severe cases, infection can lead to pneumonia, severe acute respiratory syndrome, kidney failure, and even death ^[3]^. At present, there is no specific treatment for diseases caused by novel coronavirus.

In view of the new coronavirus (COVID-19), the researchers analyzed the clinical characteristics of patients with COVID-19 and concluded that the lymphocyte count of patients, especially those with severe pneumonia, decreased significantly, while many inflammatory factors (such as IL-6, TNF-α, etc.) increased significantly, resulting in a cytokine storm (cytokine storm), leading to multiple organ failure. This is an important cause of disease progression and death ^[4]^. The Lancet published the results of minimally invasive pathological sampling of the first new type of coronary pneumonia on February 17. The patients' lungs showed diffuse alveolar injury and hyaline membrane formation, consistent with ARDS findings. The decrease in lymphocytes and the increase in highly proinflammatory CCR4+ CCR6+ Th17 cells can be found by flow cytometry. The results of pathological anatomy are of great significance for the treatment of the disease ^[5]^. We focused on the ARDS-like changes and the overactivation of Th17 cells in patients with COVID-19. Th17 cells play a role in the production of interleukin-17 (IL-17A). At present, research has revealed that the IL-17A/IL-22 axis plays an important role in maintaining the homeostasis of mucous membranes and vascular endothelial cells. Abnormal IL-17A signal transduction can lead to an excessive inflammatory response and cause acute lung injury, such as ARDS ^[6]^. Some studies have shown that the storm of cytokines in IL-17RA knockout mice is greatly weakened after infection with influenza virus. The absence of IL-17RA signaling in this model reduces pulmonary inflammation, weight loss and mortality, indicating that treatment for a variety of inflammatory mediators (including IL-17A) involved in cytokine storm early induction can effectively avoid cytokine storm mortality ^[7]^. However, the importance of Th17 cell and IL-17A participation in cytokine storm in patients with COVID-19 is still unclear. It is still unknown whether IL-17A antagonists can be used in the treatment of cytokine storm in patients with COVID-19.

Ixekizumab is a new biological agent targeting IL-17A and has the characteristics of a high clearance rate in the treatment of psoriasis ^[8]^. At the same time, its IgG4-based structure has a weak affinity for Fc γ R, and its ability to trigger antibody-dependent cell-mediated cytotoxicity (ADCC) and complement-dependent cytotoxicity (CDC) inflammatory reactions is also low ^[9]^. Based on the above findings, this study intends to explore the safety and efficacy of ixekizumab against organ injury caused by the immune response to COVID-19.

**Methods**

**Study Design**

The experiment is divided into two stages. In the first stage, the open trial, 3 patients with COVID-19 are treated with ixekizumab, and the safety and efficacy are observed for 7 days. In the second stage, 40 patients with COVID-19 are randomly divided into two groups at 1:1 for 14 days. The results of the first phase will be reported to the ethics committee for evaluation and approval, and then, the second phase of the study will be carried out. Screening for inclusion was initiated on June 2020.

**Eligibility Criteria**

The inclusion criteria for the trial are as follows: the age is 18-75 years old, regardless of sex; COVID-19 will be diagnosed by RT-PCR or gene sequencing; the clinical types are common type (including severe high-risk factors) (multiple lesions of both lungs, or lung imaging showing that the lesion progressed more than 50% within 24 to 48 hours) and severe type; an increase in IL-6 levels; and the patient voluntarily signing the informed consent form.

The exclusion criteria for the trial are as follows: severe new pneumonia infection with one of the following conditions: respiratory failure requiring mechanical ventilation, shock, ICU monitoring and treatment with other organ failure; allergy to ixekizumab or antiviral drugs; ALT/AST>5 times the ULN, neutrophils<0.5 × 10^9/^L, or platelet less than 50 × 10^9^/L; patients with impaired renal function: serum creatinine ≥2 mg/dl (176 μmol/l); complications with severe underlying diseases or a life expectancy of less than 3 months; patients with active hepatitis, definite severe bacterial or fungal infections, tuberculosis infection, or HIV infection; malignant tumors, such as lymphoproliferative diseases; active Crohn's disease; pregnant or lactating women; participation in other intervention clinical trials in the past 3 months; or other situations in which the researchers believe that it is not appropriate to join the group.

The termination standards for the trial are as follows: allergy to research drugs; judgment of the researchers that it is necessary to terminate the study ahead of time because continuing to participate in the study may bring unacceptable risks to the subjects' health based on the occurrence of serious adverse events, or the subjects are unwilling to continue to participate in the study because of the adverse events; the observation of the curative effect was affected by other diseases such as stroke in the trial; or the ethics committee or regulatory body requested that the study be suspended.

The exit standard for the trial indicates that subjects can drop out of the experiment at any time for the following reasons: the subjects withdraw their informed consent; the subjects are lost to follow-up; and the subjects ask to stop or change the medicine. During the study, when the subjects meet the above termination/withdrawal criteria, the researchers can terminate the participation of the subjects and continue the follow-up treatment and follow-up as far as possible according to the medical routine. The reason and date of the subject's withdrawal must be recorded in the case report form and the original data.

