**Treatment**

**Drugs**

Ixekizumab (*Eli Lilly and Company*): 80 mg/ml, 160 mg as a single hypodermic injection.

Antiviral treatment: according to the diagnosis and treatment plan for pneumonia related to infection by novel coronavirus of the Health Commission (trial version 6 and update).

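### Ending treatment and leaving the study are not kept apart, so the scheduled Day-7 and Day-14 CT is not secured for patients whose participation is ended after randomisation

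*Protocol*

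**What the plan says.** The relevant rules are in the termination and exit paragraphs of Eligibility Criteria.

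- **Exit reasons** include withdrawal of consent, loss to follow-up and, on the same footing, that "the subjects ask to stop or change the medicine".
- **Termination reasons** include allergy to research drugs; a judgment by the researchers that "continuing to participate in the study may bring unacceptable risks to the subjects' health based on the occurrence of serious adverse events"; that "the subjects are unwilling to continue to participate in the study because of the adverse events"; and that "the observation of the curative effect was affected by other diseases such as stroke in the trial".
- **Consequence.** When a criterion is met, "the researchers can terminate the participation of the subjects" and "continue the follow-up treatment and follow-up as far as possible according to the medical routine".
- **Data required at that point.** "The reason and date of the subject's withdrawal must be recorded in the case report form and the original data". No other item is made mandatory.

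Elsewhere, Primary outcomes defines the primary outcome as change in CT score at Day 7 and at Day 14 or discharge, read blind by outside experts. Enrollment and follow-up schedules the scans, laboratory tests, dyspnea score and blood gases at those visits. Secondary outcomes adds the 7-point clinical status scale and 14-day mortality. Drugs gives ixekizumab as "160 mg as a single hypodermic injection". Analysis of curative effect uses both FAS and PPS and makes the PPS the main efficacy set.

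**The concern.** Stopping a treatment and leaving a study are different events. Here the first is a ground for the second, and what follows is routine care, not the trial's visits. The protocol does not say that the Day-7 and Day-14/discharge CT still takes place.

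The reasons arise after randomisation. Allergy, adverse events and drug changes are plausibly linked to treatment. An intercurrent disease is a post-randomisation event, and its ground for termination is its effect on what is observed. Only the CT reading is blinded; patients and treating staff know the arm, so a discretionary decision to end participation can fall unevenly between arms. Blind reading does not help with a scan that was not taken.

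Because ixekizumab is a single injection, a patient who changes medicine after dosing can only be changing the antiviral or other drugs. That patient has already received the study drug and can still be measured.

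This is a rule about conduct and data collection. A statistical analysis plan written later can choose how to handle missing scans, but it cannot recover them.

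**Working it through.** **1. The plan's own figures.** Stage 1 has 3 patients and stage 2 has 40: 3 + 40 = 43, as stated under Sample Size Projections. Allocation is 1:1, so 40 / 2 = 20 per arm. The protocol gives no SD, expected effect or dropout rate and says that the sample size was not statistically estimated. The size of any bias therefore cannot be derived from it.

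**2. The rules set side by side.**

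| Question | What the text supports |
|---|---|
| Does stopping or changing medicine count as a study exit? | Yes, it is an exit reason |
| Is exit automatic? | No, it is discretionary |
| Does a serious adverse event alone end participation? | No, it needs a judgment of unacceptable risk or the patient's unwillingness |
| Is some follow-up foreseen afterwards? | Yes, as far as possible, under routine care |
| Are the scheduled Day-7 and Day-14/discharge CT required afterwards? | Not stated |
| What must be recorded at withdrawal? | Reason and date |

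The supportable conclusion is that the data are not secured, not that they are certain to be lost.

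**3. Illustration of size (assumptions, not document figures).** Let k of 20 patients in one arm have no CT, and let their mean CT change be g SD worse than that of the arm's remaining patients. The full-arm mean is (1 − k/20) × remaining mean + (k/20) × lost mean. The observed arm mean therefore differs from the full-arm mean by:

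shift = (k/20) × g

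With losses in both arms, the net shift is (k₁/20) × g₁ − (k₀/20) × g₀.

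For the chance of a false positive when there is no true difference, take a two-sided 5% test, a normal approximation and standard error √(1/20 + 1/(20 − k)) in SD units.

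| k lost, one arm only | g (SD) | Shift (SD) | Approximate type I error |
|---|---|---|---|
| 2 | 0.5 | 2/20 × 0.5 = 0.05 | 5.3% |
| 2 | 1.0 | 2/20 × 1.0 = 0.10 | 6.1% |
| 2 | 1.5 | 2/20 × 1.5 = 0.15 | 7.5% |
| 4 | 0.5 | 4/20 × 0.5 = 0.10 | 6.0% |
| 4 | 1.0 | 4/20 × 1.0 = 0.20 | 9.2% |
| 4 | 1.5 | 4/20 × 1.5 = 0.30 | 14.5% |

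If k and g are equal in both arms, the net shift is 0. If the lost patients would have fared better, the sign reverses.

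**The case against.** The case on the other side has several parts, and most of them limit the point without removing it.

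- **Discretion.** A reader might infer that anyone with a serious adverse event or a drug change leaves and that the primary data are then lost. The text does not support this. Termination is permitted, not required, and a serious adverse event needs a further judgment or the patient's own unwillingness. This stands, and it limits the point to a risk of loss. Discretion in an open trial does, however, leave room for decisions that differ by arm.
- **Follow-up continues.** Routine care may well yield a CT, and scans taken before exit are kept. This also stands. Routine care still does not secure a scan at the scheduled time for the blind reading.
- **The stroke criterion.** A reader might take it as removing patients because their COVID-19 went badly. It speaks of other diseases, and no link to a worse CT score is given. That reading should not be used.
- **Safety and mortality counts.** A reader might conclude that these are biased. The event that triggers termination comes before it and remains recordable, the reason must be documented, and bacterial or fungal infections are followed until cured or stable. Only later events and vital status are at risk.
- **Direction.** It is tempting to say that the arm with more terminations is favoured. That holds only if the lost patients would have done worse, which the document does not show.
- **Exploratory study.** With 43 patients and no formal sample-size estimate, less rides on the test. But with 20 per arm each missing scan is 1/20 = 5% of the arm, so completeness matters more, not less.

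Withdrawal of consent and true loss to follow-up are legitimate exits and are not criticised here.

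**Conclusion.** The point holds in a limited form. The protocol does not separate stopping treatment from leaving the study, and after a discretionary termination it does not secure the primary CT assessments or the later clinical-status, safety and vital-status data. Because the grounds arise after randomisation in an open-label trial, the loss can differ by arm and the CT comparison may be biased.

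How large the bias would be, and in which direction, is unknown. The 0.05 to 0.30 SD range rests wholly on assumed one-sided losses of 2 to 4 of 20 and an assumed gap of 0.5 to 1.5 SD. Making the PPS the main efficacy set adds to the difficulty, since patients whose participation ended may be left out of it even if they were scanned. Moving to the FAS alone would not restore scans that were never taken. The matter should be corrected; it does not by itself invalidate the trial.

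**What to change.** Amend the termination and exit paragraphs as follows.

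1. State that stopping or changing treatment, or an intercurrent illness, does not end data collection.
2. Unless consent to follow-up is withdrawn, every randomised patient has the already scheduled Day-7 and Day-14/discharge CT, laboratory tests, clinical-status scale, adverse-event recording and 14-day vital status.
3. Record an intercurrent illness such as stroke as an adverse event, so that it is not a reason to stop collecting data.
4. In Analysis of curative effect, state that these patients are included in the FAS comparison, and report that comparison as the main CT result or at least alongside the PPS. Without this step, the extra scans might never enter the main comparison.

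Clinical rules on stopping treatment stay unchanged; the amendment concerns data collection and analysis only.

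The cost is protocol wording and a few scheduled assessments in patients who have stopped treatment, within a 14-day trial in which most patients are likely still to be in hospital.

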**Research center**

This experiment adopts a multicenter design. The first stage is carried out in Xiangya Hospital of Central South University, and the second phase is carried out simultaneously in the third Xiangya Hospital of Central South University.

**Randomization**

The first stage is an open design. In the second stage, central randomization is used, and the eLite random system of Nanjing Medical University is used. The main efficacy indicator CT results will be evaluated by the third-party blind method outside the research team.

**Baseline Procedures**

The following assessments must be completed during the screening period: medical history, occupational history, drug history, hobbies and smoking history; vital signs: respiratory rate, heart rate, and blood pressure; clinical symptom evaluation: dyspnea score; routine laboratory examination: routine blood tests, routine urine tests, liver and kidney function, blood glucose, electrolytes, troponin, serum ferritin, CRP, IL-6, TNF-α, PCT and T cell subsets; arterial blood gas analysis: pH, PaO2, PaCO2 and oxygenation index; routine electrocardiographic examination (ECG); chest high-resolution CT (HRCT) examination and score; and APACHE II score.

**Enrollment and follow-up**

Those who meet the enrollment criteria will enter the intervention:

On the 3rd day of enrollment, the following procedures will be performed: (1) record concomitant medication; (2) record adverse events; and (3) carry out CT examination.

On the 7th day (±1 day)), the following procedures will occur: (1) record the combined use of drugs; (2) record adverse events; (3) measure vital signs: respiratory rate, heart rate and blood pressure; (4) evaluate clinical symptoms: dyspnea score; (5) perform routine laboratory examination: routine blood, routine urine, liver and kidney function, blood glucose, electrolyte, troponin, hypersensitive CRP, procalcitonin, serum ferritin; (6) assess inflammation index (CRP, IL-6, TNF- α), infection index (routine blood tests, PCT) and immune function (T cell subsets); (7) analyze arterial blood gas: pH, PaO2, PaCO2 and oxygenation index; (8) perform HRCT examination and score; and (9) calculate APACHE II score.

Fourteen days after admission (±3 days) or discharge, (1) record the combined use of drugs; (2) monitor possible adverse reactions to ixekizumab; (3) check vital signs: respiratory rate, heart rate, blood pressure; (4) evaluate clinical symptom: dyspnea score; (5) perform routine laboratory examination: routine blood, routine urine, liver and kidney function, blood glucose, electrolyte, troponin, hypersensitive CRP, procalcitonin, serum ferritin; (6) assess inflammation index (CRP, IL-6, TNF-α), infection index (routine blood, PCT) and immune function (T cell subsets), and so on; (7) analyze arterial blood gas: pH, PaO2, PaCO2 and oxygenation index; and (8) perform HRCT examination and score; (9) APACHE Ⅱ score was calculated (Figure 1).

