**Security assessment**

**Safety index**

The incidence of adverse events/serious adverse events; laboratory examination (blood routine, blood biochemistry, urine routine), vital signs, physical examination and electrocardiogram before and after treatment.

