**Security Analysis.**

Safety evaluation analysis: Safety indicators include adverse events/important adverse events/serious adverse events, laboratory examination, vital signs, physical examination and electrocardiogram and other clinically significant changes. According to the cases of adverse events that occur during the SOC/PT summary trial, the cases and incidence of adverse events between the two groups will be summarized and compared. Descriptive statistical laboratory examination and other indicators, if necessary, compare the changes between the two groups and describe the abnormal cases before and after treatment.

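### The Day 14/discharge visit list asks only for ixekizumab reactions, which contradicts the planned comparison of all adverse events between the arms

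*Protocol*

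**What the plan says.** All references are to the protocol.

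- **Enrollment and follow-up, Days 3 and 7.** Both lists carry the same arm-neutral item: "2) record adverse events".
- **Enrollment and follow-up, last visit.** The visit is timed as "Fourteen days after admission (±3 days) or discharge". In the same position its list has "monitor possible adverse reactions to ixekizumab", and no other item on it records adverse events. Vital signs, routine blood and urine tests and biochemistry are listed for everyone.
- **Safety index.** The first measure is "The incidence of adverse events/serious adverse events", with no limit by arm or causality. It also lists "vital signs, physical examination and electrocardiogram before and after treatment".
- **Security Analysis.** Here "the cases and incidence of adverse events between the two groups will be summarized and compared".
- **Treatment Protocols.** Stage 2 randomises 40 patients 1:1, so 20 per arm. Controls receive antiviral therapy without ixekizumab.
- **Randomization.** The only assessment stated to be blinded is the CT reading.
- **Figure 2.** A line giving safety and efficacy assessment at Days 0, 3, 7 and 14 appears twice, matching the two randomised arms.
- **Report and follow-up of adverse events and serious adverse events.** The instructions are general and make no distinction by arm.

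**The concern.** A between-group comparison of adverse event incidence needs the same question put to both arms over the same period. The last visit list departs from this in two ways. It names a drug that only one arm receives, so taken at its word it elicits nothing from a control patient. And for ixekizumab patients it replaces all events with those thought possibly due to the drug, a judgement made by staff who know the allocation. Reactions to the antivirals, which both arms receive, fall outside the item altogether.

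Safety is half of the trial's stated aim. An event that was never elicited cannot be recovered by any later analysis, so a statistical analysis plan could not repair this. The visit lists are also the most specific collection instruction in the protocol. Since the Research center section names two hospitals, one could follow the list and the other the flow diagram.

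**Working it through.** **Step 1: the texts side by side.** The protocol states no adverse event rate, test or significance level for safety, so there is no figure to reproduce. The check is first one of wording.

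| Place | What is collected or analysed | Limited by arm or causality? |
|---|---|---|
| Visit list, Days 3 and 7 | adverse events | no |
| Visit list, Day 14/discharge | possible reactions to ixekizumab | yes, both |
| Safety index | incidence of adverse and serious adverse events | no |
| Adverse event reporting section | adverse and serious adverse events | no |
| Security Analysis | incidence compared between groups | no |
| Figure 2 | safety assessed through Day 14, both arms | no |

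One row disagrees with the other five.

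**Step 2: what the literal reading could do (illustration on assumed rates).** Let *p* be the risk of at least one adverse event in a week, the same in both arms and in both weeks. This is an assumption, taken from 20% to 40%. Let *c* be the share of second-week events that is recorded in an arm. Then

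recorded two-week incidence = 1 − (1 − p)(1 − p·c).

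With full recording (c = 1) the true incidence is 1 − 0.8² = 0.36 at p = 0.20 and 1 − 0.6² = 0.64 at p = 0.40. With no second-week recording (c = 0) it is simply p. With half recorded (c = 0.5) it is 1 − 0.8 × 0.9 = 0.28 and 1 − 0.6 × 0.8 = 0.52.

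| Second-week recording | Ixekizumab minus control, p = 0.20 | p = 0.40 |
|---|---|---|
| Ixekizumab all, control none | 0.36 − 0.20 = +16 points | 0.64 − 0.40 = +24 points |
| Ixekizumab half, control none | 0.28 − 0.20 = +8 | 0.52 − 0.40 = +12 |
| Same rule in both arms | 0 | 0 |
| Ixekizumab half, control all | 0.28 − 0.36 = −8 | 0.52 − 0.64 = −12 |
| Ixekizumab none, control all | 0.20 − 0.36 = −16 | 0.40 − 0.64 = −24 |

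The true difference is zero in every row. With 20 per arm, 16 points is 3.2 patients and 24 points is 4.8. If second-week events are missed in both arms, the difference is zero but both incidences are too low by 16 to 24 points.

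**Step 3: sensitivity.** Let the first-week risk vary over 20–40%, the second-week risk over 10–30% and ixekizumab capture over 50–100%, with no control capture. The false difference, (1 − p_early) × p_late × c, then runs from 0.6 × 0.1 × 0.5 = 3 points to 0.8 × 0.3 × 1 = 24 points. By exact enumeration with 20 per arm, a two-sided Fisher test at 0.05 (also assumed) would reject with probability 0.03 to 0.27. When the recorded rates are equal, that test rejects with probability at most 0.05.

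**Step 4: ECG and physical examination.** The safety index claims both before and after treatment. In the visible text ECG appears only under Baseline Procedures, and physical examination is on neither the baseline list nor any follow-up list. This affects both arms alike and is unrelated to the asymmetry.

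**The case against.** The strongest reply is that the protocol, read as a whole, points to symmetric collection. The safety index, the adverse event reporting section and the safety analysis carry no limit by arm. Figure 2 shows safety assessment at Day 14 in both arms. Laboratory tests and vital signs are taken from everyone at the last visit, so abnormalities there would be seen in controls too. A list of visit procedures is also not a rule that events between visits go unrecorded.

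Most of this stands. A reader might infer from the Day 14 item that only ixekizumab reactions are collected after Day 7 and that the comparison is therefore asymmetric as a settled matter. The documents do not support that: the other sections contradict it, and nothing suggests that one-arm collection was chosen. A reader might also infer that the bias must count against ixekizumab. That does not follow either, since controls could be recorded under the general reporting section while ixekizumab events pass through a causality filter.

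The reply does not remove the contradiction. Figure 2 does not say what is recorded, and the reporting section deals with how events are diagnosed, named and followed rather than when they are elicited.

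On ECG and physical examination, Figure 1 is not shown and may carry entries that the text lacks. It would go too far to say that no post-treatment values will exist; what the visible text lacks is a visit for them.

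**Conclusion.** The point holds as an internal contradiction. The last visit list does not supply the data that the safety index and the between-group analysis require, while other sections suggest that all events in both arms were meant. If the list is followed literally, late adverse events are ascertained by arm-dependent rules and the comparison is biased in a direction that cannot be known in advance.

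The 16 to 24 points are a worst case. They rest on assumed weekly risks of 20% to 40%, on complete recording in one arm and none in the other during the second week, and on everyone having a full second week, although follow-up can end at discharge. Less extreme assumptions give as little as 3 points. The blinded CT primary outcome is not affected.

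The ECG and physical examination mismatch is a separate, minor scheduling inconsistency, subject to what Figure 1 shows.

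**What to change.** In Enrollment and follow-up, replace the Day 14/discharge item with the arm-neutral item used at Days 3 and 7, apply it to both arms, and record the judged relation to study drug as a separate field. Whatever the event rate, the ascertainment rule is then the same in both arms. Reactions to ixekizumab can still be summarised from the causality field.

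Separately, reconcile the Safety index section with Baseline Procedures and the follow-up lists, so that every measure claimed before and after treatment either has a stated visit or is no longer claimed.

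The cost is a change of wording and a matching change to the case report form. No change to treatment, sample size or the primary outcome is involved. It needs to be made before the last visits take place, because late events that were not elicited cannot be reconstructed.
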